#### Coronary CT protocol

All coronary CTA studies are acquired with a multidetector CT scanner (Discovery HD 750; Gemstone Spectral Imaging, GE Healthcare, Milwaukee, WI, USA). During scanning, participants hold their breath and are still. To obtain better image quality for each contrast agent, scans are performed with different protocols depending on whether high- or low- concentration contrast agents are used. If a high-concentration contrast agent (iopamidol 370 mgI/ml) is used, scans are conducted at 120 kVp for higher BMI (27 < BMI < 35) patients and at 100 kVp for lower BMI (15 < BMI ≤ 27) patients, with adjusted mAs (BMI-based tube potential selection). If a low-concentration contrast agent (iodixanol 270 mgI/ml or iodixanol 320 mgI/ml) is used, scans are conducted 20 kVp lower than in the BMI-based tube potential protocol: that is, at 100 kVp for higher BMI and 80 kVp for lower BMI. A beta-blocker is used for patients with a heart rate higher than 60 beats per minute. Scans initiate a bolus tracking method with a 4.8-s delay after reaching 100 Hounsfield units (HU) in the ascending aorta enhancement.

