#### Myocardial perfusion CT

Stress myocardial perfusion CT will be performed in patients with at least one segment of greater than 50 % stenosis on coronary CT angiography. A static CT perfusion protocol will be used, and stress will be induced by infusing 140 mcg/kg/min adenosine under ECG monitoring for up to 6 min. The randomly assigned contrast agent, which was used for coronary CT angiography in the patient, will be injected 4 min 30 s after the adenosine injection, using the same injection method for contrast agent and image acquisition settings as used for the coronary CT angiography with the only difference being an additional scan delay of 2 s.

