#### Secondary efficacy analysis

Qualitative evaluation of the image quality of the coronary artery will be performed. Two experienced observers will review all coronary CT images and score the image quality for each segment with a 4-point grading system on visual assessment: Grade 1, nondiagnostic; Grade 2, reduced image quality; Grade 3, nonlimiting artifacts; and Grade 4, complete absence of motion artifacts with good attenuation of the vessel lumen and clear delineation of the vessel walls with the additional ability to assess luminal stenosis.

Quantitative evaluation of image quality of perfusion CT will be performed. The myocardium will be divided into 16 segments according to AHA classification, and the HU value of each segment will be measured. Mean HU value, SNR, and CNR of myocardial enhancement will be compared between the different arms of the trial.

Diagnostic accuracy of coronary CT angiography compared to invasive coronary angiography will be calculated. Segment-basis analysis, sensitivity, specificity, positive predictive value, negative predictive value, and accuracy of CT angiography for diagnosis of the presence of CAD defined by more than 50 % diameter stenosis compared to invasive coronary angiography will be calculated and compared between the different concentrations of contrast agent by means of a generalized estimating equation based on a binary logistic model.

Quantitative evaluation of image quality of coronary artery will be performed on a per-vessel and per-segment basis.

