#### Primary statistical analysis

Per-protocol analysis will be performed primarily; an additional intention-to-treat analysis will be also performed. The 98.33 % confidence interval (CI) for the difference of mean contrast enhancement in the ROIs will be calculated. The noninferiority of the low-dose group compared to the high-dose group will be demonstrated if the lower bound of the two-sided 98.33 % CI lies above the pre-specified noninferiority margin. Because missing values are expected for 5 % or fewer of the participants, we have planned complete-case analysis for the primary analysis. To account for multiple observations per patient in secondary analysis, we will use a linear mixed model, including fixed effects for the group and random intercepts for the patient. Patients with a missing observation in some vessel or segment will be included in the per-vessel and per-segment analysis by using the linear mixed model. Analysis of covariance (ANCOVA) with BMI as a covariate will be used to compare the mean HU of the myocardium on static perfusion CT. Inter-reader agreement for the assessment of image quality will be evaluated using a linearly weighted kappa statistic. Analysis of variance (ANOVA) will be used to compare mean changes in heart rate before and after CT examinations among the three groups. To compare the diagnostic accuracy of invasive coronary angiography for diagnosis of significant coronary artery stenosis with more than 50 % stenosis among the three groups, logistic regression analysis using a generalized estimating equation (GEE) will be used to account for the correlation among multiple segments within the same subject. All statistical analyses will be performed using SAS (SAS Ver. 9.2; SAS Institute, Cary, NC, USA) and two-sided *P* values less than 0.05 will be considered statistically significant.

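### The myocardial ANCOVA names BMI as its only covariate although tube potential steps at BMI 27 in every arm; a linear BMI term takes up only about half of that step, at a modest cost in precision

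*Protocol article*

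**What the plan says.** All places are in the Protocol article.

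- **Model.** Statistical methods, Primary statistical analysis: "Analysis of covariance (ANCOVA) with BMI as a covariate will be used to compare the mean HU of the myocardium on static perfusion CT". The section does not say how BMI is coded.
- **Tube potential, 370 mgI/ml arm.** Coronary CT protocol: scans are "at 120 kVp for higher BMI (27 < BMI < 35) patients and at 100 kVp for lower BMI".
- **Tube potential, 270 and 320 mgI/ml arms.** Same section: scans are "at 100 kVp for higher BMI and 80 kVp for lower BMI".
- **Perfusion CT.** The section Myocardial perfusion CT carries these settings over, "using the same injection method for contrast agent and image acquisition settings as used for the coronary CT angiography", apart from a longer scan delay. It also limits who is scanned: "Stress myocardial perfusion CT will be performed in patients with at least one segment of greater than 50 % stenosis on coronary CT angiography". No expected number is given.
- **Status.** Secondary efficacy analysis: "Mean HU value, SNR, and CNR of myocardial enhancement will be compared between the different arms of the trial".
- **Allocation.** Randomization is 1:1:1 by site; no BMI stratum is mentioned.

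**The concern.** The trial rests on the premise that a lower tube potential raises enhancement (Background; Discussion). On that premise, HU should drop where the protocol raises the tube potential, which is at BMI 27 in each arm. The analysis adjusts for BMI, the variable that drives the change, but not for the cut-point at which it happens. A straight line in BMI follows the general trend across the cut and misses the jump itself. What it misses adds to the residual variance, and chance differences between arms in the share of patients above 27 are corrected only in part. At stake is the precision of the myocardial comparison, in a subset whose size is not stated.

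**Working it through.** **Plan's own figure.** There is none to reproduce: the article gives no sample size, SD or power for the myocardial analysis. The 106 per group belongs to the coronary primary endpoint and does not enter here.

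**Inputs.** From the article: the cut at 27, a 20 kVp change at the cut in each arm, and BMI as the only named covariate. Assumed, because the article gives nothing: BMI normal with mean 24.8 and SD 3.4; BMI entered linearly; a step of *s* residual SD, equal in all arms.

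**1. Share of the step absorbed by linear BMI.** Let I = 1 if BMI > 27.
- z = (27 − 24.8)/3.4 = 0.647, so p = P(BMI > 27) = 0.259.
- Var(I) = p(1 − p) = 0.192.
- The normal density at z is 0.324, so the squared correlation of BMI with I is 0.324²/0.192 ≈ 0.55.

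About 55 % of the step variance is absorbed and about 45 % is left.

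**2. Cost in precision.** With residual variance 1, the variance left over is s² × 0.192 × (1 − 0.546) = 0.0871 s².

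| Step (residual SD) | Left over | Cut in residual variance from adding the stratum | SE ratio, √(1 + left over) |
|---|---|---|---|
| 0.5 | 0.022 | 2 % | 1.01 |
| 1.0 | 0.087 | 8 % | 1.04 |
| 1.5 | 0.196 | 16 % | 1.09 |

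**3. Sensitivity to the BMI distribution.** With the mean between 23 and 26 and the SD between 2.5 and 4, truncated to 15–35, linear BMI absorbs 24–63 % of the step variance. The SE rises by 0.5–1.1 % for a step of 0.5 and by 1.9–4.4 % for a step of 1.0. For a step of 1.5, the left-over variance at step 1.0 (0.0393 to 0.0901) is multiplied by 2.25, which gives 0.088 to 0.203 and an SE rise of about 4–10 %.

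**4. Is a step of this size plausible?** Only an indirect indication is available, from coronary figures. The sample-size section assumes equal mean HU in all arms, although the low-concentration arms are scanned at 20 kVp less. If HU is proportional to iodine (assumed), 20 kVp more at fixed iodine lowers HU by 1 − 320/370 = 13.5 % to 1 − 270/370 = 27.0 %. The margin of 51.26 HU is stated to be 9 % of a reported mean, which implies 51.26/0.09 = 569.6 HU. The step is then 77 to 154 HU, or 0.65 to 1.29 times the planning SD of 118.93. Taking the article's other mean, 439.96 HU, gives 0.50 to 1.00 SD. Myocardial values may differ.

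**5. Cost of the extra term if there is no step.** With 15 per arm (45 patients), the present model has 41 error degrees of freedom. One superfluous covariate raises the variance of the arm difference by about 1/40 = 2.5 %, or 1.2 % in SE. With 30 per arm (86 error degrees of freedom) it is about 1/85 = 1.2 %, or 0.6 % in SE. Break-even, where 0.0871 s² equals this cost, is at s ≈ 0.54 and s ≈ 0.37.

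**6. Simulation.** Setup: BMI mean 24.5, SD 3, slope −0.05 SD per unit, 4,000 runs, true arm difference 0.75 SD, two-sided 5 % test. Subset sizes are assumed.

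| Per arm | Step | Power, BMI only | Power, BMI and stratum |
|---|---|---|---|
| 15 | 0.5 | 49.0 % | 49.1 % |
| 15 | 1.0 | 48.5 % | 50.4 % |
| 30 | 0.5 | 79.5 % | 80.0 % |
| 30 | 1.0 | 78.6 % | 81.0 % |

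For a step of 1.5, with mean 24.8 and SD 3.4, the gain is about 6 to 7 points. With no true arm difference and an equal step, rejection stayed near 5 % and the mean estimate near zero under both models.

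**7. Unequal steps.** With steps of 0.7 SD in the 370 mgI/ml arm and 1.0 SD in the others, the mean estimate was −0.055 SD with BMI alone and −0.053 SD with the stratum added. This is close to the average difference built in, 0.3 × 0.202 = 0.06 SD below zero. Rejection was 5.2 % under both models.

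**The case against.** The strongest reply is that the article fixes nothing wrongly. It names BMI without saying that it enters linearly, and coding can be left to an analysis plan that is not shown. BMI also determines the tube potential within each arm, so the right variable is already in the model. What stands: the point depends on the usual reading of a BMI covariate as one linear term, and even that term removes a large part of the step. What does not stand: the cut-point is a feature of the protocol's own design, and the covariate set as written leaves it out.

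Three stronger readings are tempting, and the documents do not support them.

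- **That the whole step stays in the error term.** It does not; about half is absorbed.
- **That the arm comparison is biased or its test invalid.** With an equal step and arms of comparable BMI distribution, neither occurs, and chance imbalance is already reflected in the standard error. Two caveats remain. The subset is selected after randomization, on a scan made with the assigned agent, so comparable BMI is not guaranteed. The steps (100 to 120 kVp in one arm, 80 to 100 kVp in the others) may also differ in HU. The article gives no figures showing that either happens.
- **That the subset is small and the loss large.** No subset size is stated, and the largest figures here need an assumed step of 1.5 SD.

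It is also fair to say that a single common stratum term is itself an approximation if the steps differ between arms.

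**Conclusion.** The point holds as a minor matter of efficiency in a secondary analysis. With linear BMI alone, roughly half of any step in myocardial HU at BMI 27 remains as error. The standard error is about 1 %, 4 % or 9 % larger than necessary for steps of 0.5, 1.0 or 1.5 residual SD. At steps up to 1.0 SD, adding the stratum gains between almost nothing and about 2.5 points of power at 15 to 30 patients per arm. The BMI distribution, step size, subset size and linear coding are all assumptions. The primary noninferiority test on coronary HU is not affected.

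**What to change.** State that the myocardial ANCOVA includes arm, BMI as a continuous covariate, and BMI stratum (≤27 / >27) as a factor. Use the stratum and not the kVp actually applied. Adjusting for actual kVp would remove from the arm comparison the 20 kVp difference that is part of the low-concentration strategy. If the step may differ between the 370 mgI/ml arm and the other two, an arm-by-stratum interaction can be given as a sensitivity analysis.

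The cost is one degree of freedom, with data already collected and no change to trial conduct. If there is no step or only a small one, the loss is negligible: about 1 % in the standard error at 15 per arm and about half that at 30.

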### Randomization

All enrolled subjects are randomly assigned to one of three concentrations of contrast agent in a 1:1:1 ratio based on each trial site. We use concealed allocation and an adequate computer-generated allocation sequence to avoid selection bias. Thus, neither the patient nor the outcome assessor knows to which group the patient is allocated. Therefore, if unblinding is deemed necessary, any of the investigators, coordinators, or CT operators can provide the information of the contrast agent used. If the assessors of the outcome learn this information, they should report this on the corresponding case report form.

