#### Preparation of patients

If participants do not have contraindications for the use of the nitroglycerine, they receive sublingual nitroglycerine before coronary CT angiography. If a participant’s heart rate is equal to or greater than 60 beats per min, a beta-blocker is administered. If > 50 % stenosis is apparent on the coronary CT angiography, participants will undergo stress perfusion CT. In these cases, nitroglycerine and beta-blockers are not used. Separate intravenous lines are secured for the injection of adenosine and contrast media.

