### Data management

The data-coordinating center in Severance Hospital is collecting data through a secure Internet connection to the central server and monitoring the overall dataset. At the start of the trial, the monitors conducted a tutorial on the web-based data entry system and the image upload system. They will audit the overall quality and integrity of the data regularly every 6 months and, if necessary, contact the site investigator and coordinator to review and confirm the correctness of the data with source data in compliance with the protocol. The monitors will verify that all adverse events were documented in the correct format and are consistent with protocol definition. The monitor conducts the monitoring procedure independently from the investigators and the sponsor. The primary and secondary endpoints in this trial include only the image quality and not the patients’ clinical outcomes. If the quality is not enough to determine significant coronary artery disease due to insufficient enhancement from a low-concentration contrast agent, repeat examination with a high-concentration contrast agent can be used at the site investigator’s discretion. Therefore, the conduct of an interim analysis is not needed to evaluate any potentially important reasons to modify or discontinue the trial. Adverse effects and serious adverse events will be recorded in the case report form. A summary of adverse effects and serious adverse effects will be immediately forwarded the independent Institutional Review Board and local health authorities, according to local regulations.

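### Heart-rate change is compared by ANOVA without the pre-scan heart rate as covariate: a valid test, but less precise than an ANCOVA on the same data

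*Protocol article*

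**What the plan says.** The protocol article mentions the heart-rate analysis once, under Primary statistical analysis: "Analysis of variance (ANOVA) will be used to compare mean changes in heart rate before and after CT examinations among the three groups". No adjustment is attached to it. The general rule at the end of that section applies, under which "two-sided *P* values less than 0.05 will be considered statistically significant".

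The same section specifies covariate adjustment for a different outcome: "Analysis of covariance (ANCOVA) with BMI as a covariate will be used to compare the mean HU of the myocardium on static perfusion CT".

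Heart rate is not listed under Primary efficacy analysis or Secondary efficacy analysis. The Data management section limits the endpoints: "The primary and secondary endpoints in this trial include only the image quality and not the patients’ clinical outcomes".

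On allocation, the Randomization section says: "All enrolled subjects are randomly assigned to one of three concentrations of contrast agent in a 1:1:1 ratio based on each trial site".

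**The concern.** Subtracting the pre-scan value is often taken to deal with baseline differences. It does so fully only if each extra beat before the scan goes with exactly one extra beat after it. When the slope of post on pre is below 1, as is usual for a repeated measurement, the change score over-corrects. An arm that happens to start higher then shows a larger fall, whatever the contrast agent did. The between-arm estimate therefore carries part of any chance baseline difference, and its variance is larger than the collected data require.

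The covariate needs no new data collection, since a change is defined only where a pre-scan value exists. What is at stake is the precision of one three-arm comparison, not its validity.

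**Working it through.** **Inputs.**
- Planned method: ANOVA of change across three arms, no covariate (Primary statistical analysis).
- Group size: 106 per arm with 10% dropout (Sample size and power calculation), so 106 × 0.9 ≈ 95 evaluable per arm.
- Heart-rate SD and pre/post correlation rho: not given. SD is set to 1, so results are in SD units. rho is an assumption, shown over 0.3 to 0.9.
- Assumption: equal pre- and post-scan variance σ².

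The article gives no power or precision figure for heart rate, so there is none to reproduce.

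**Step 1: variance per patient.**
- Change score: Var(post − pre) = σ² + σ² − 2·rho·σ² = 2(1 − rho)σ².
- ANCOVA, residual after regressing post on pre: (1 − rho²)σ².
- Ratio: (1 − rho²) / [2(1 − rho)] = (1 + rho)/2.

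The variance of a between-arm difference multiplies both by 2/n, so the ratio also holds for the comparison of arms.

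**Step 2: carry-over of baseline imbalance.** The change score fixes the slope of post on pre at 1, while under equal variances the actual slope is rho. A baseline difference of 1 SD between two arms therefore shifts the change-score difference by −(1 − rho) SD. With ANCOVA the expected shift is 0. The SD of the chance imbalance between two arms of 95 is √(2/95) ≈ 0.145 SD, so a typical carry-over is 0.145 × (1 − rho).

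| rho (assumed) | Change variance | ANCOVA variance | Ratio | Patients per arm under ANCOVA matching 95 under change scores | Shift per 1 SD imbalance | Typical carry-over (SD) |
|---|---|---|---|---|---|---|
| 0.3 | 1.40 | 0.91 | 0.65 | 62 | −0.7 | 0.10 |
| 0.5 | 1.00 | 0.75 | 0.75 | 71 | −0.5 | 0.07 |
| 0.7 | 0.60 | 0.51 | 0.85 | 81 | −0.3 | 0.04 |
| 0.8 | 0.40 | 0.36 | 0.90 | 86 | −0.2 | 0.03 |
| 0.9 | 0.20 | 0.19 | 0.95 | 90 | −0.1 | 0.015 |

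The patients column is 95 × ratio.

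**Step 3: check by simulation.** Three arms of 95, no true arm effect, 4000 runs at each rho:

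| rho | Variance ratio | Slope of change-score estimate on imbalance | Slope of ANCOVA estimate on imbalance | Type I error, ANOVA | Type I error, ANCOVA |
|---|---|---|---|---|---|
| 0.5 | 0.77 | −0.49 | 0.01 | 0.048 | 0.054 |
| 0.7 | 0.86 | −0.29 | 0.01 | 0.049 | 0.044 |
| 0.9 | 0.94 | −0.11 | −0.02 | 0.050 | 0.051 |

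Ratios and slopes agree with the formulas. Both tests hold the nominal 5%.

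**Step 4: unequal variances.** In general, change-score variance minus ANCOVA variance equals (σ_pre − rho·σ_post)². This is never negative, and it is zero only when the slope of post on pre is exactly 1. The direction of the result therefore does not depend on equal variances; its size does.

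**The case against.** The strongest objection is that nothing here is wrong. Under randomisation, ANOVA of change is unbiased, and its standard error already reflects chance baseline imbalance. The simulation confirms that type I error is kept. Heart rate is not an endpoint, and the trial is sized on HU alone. Two heart rates taken in the same patient around one scan may correlate strongly, and at rho 0.9 the gain is only 5%. All of this stands, and it limits the point to a gain in precision.

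A further objection is that details of a supporting analysis may be left to a plan that is not shown. This stands only in part, because the article does fix the method by naming ANOVA.

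Three stronger readings are tempting but not supported:

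- **That this comparison is the trial's evidence on why iso-osmolar agents may give better images.** The Discussion raises heart rate there to explain the result of an earlier four-concentration study, and it speaks of variability, not mean change. The objectives and the primary hypothesis say nothing about heart rate.
- **That beta-blocker use makes the change strongly dependent on baseline.** Preparation of patients says that when the rate is "equal to or greater than 60 beats per min, a beta-blocker is administered". The inference needs the pre-scan reading to precede the drug, and the article does not state that order. Table 2 lists two sets of vital signs at the CT angiography visit, without timing relative to drug or scan and without naming heart rate.
- **That the ANCOVA for myocardial HU makes the plan inconsistent.** That model adjusts for BMI, which determines tube potential under Coronary CT protocol and so bears directly on HU. It implies no general policy of baseline adjustment.

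**Conclusion.** The point holds as a minor improvement in efficiency. The planned ANOVA is valid but gives up precision that the pre-scan heart rate would supply, and its estimate moves with chance baseline imbalance. ANCOVA would reduce the variance by 5% to 35% for rho from 0.9 down to 0.3. This rests on an assumed rho, equal pre- and post-scan variances, and about 95 evaluable patients per arm. The direction is secure in large samples. The size is not known from the article and may be small if the two readings correlate strongly.

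A reader might infer a bias or an inflated error rate; neither follows. The primary HU comparison, its margin and the sample size are unaffected.

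**What to change.** Replace the ANOVA of change by an ANCOVA with arm as factor and pre-scan heart rate as covariate. The outcome may be post-scan heart rate or change, since both give the same arm differences once the pre-scan value is in the model. Site can be added as a factor, because randomisation is by site.

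The cost is one line of analysis text and one degree of freedom for the covariate, plus those for site if it is included. No additional data are needed. The change should be made before the data are analysed, so that the choice between the two models is not made with results in view.
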